### Setting and participants

#### Recruitment of clusters

The local research teams in Chile and Argentina will contact alumni offices at universities, personnel departments at healthcare centres and human resources managers in large companies to invite individuals to participate in the study. Representatives from these organisations will be interviewed and provided with a Plain Language Statement prior to participant recruitment and randomisation. Multiple meetings with representatives from each setting are planned in order to minimise the influence of organisational interests on the recruitment of participants. We anticipate conducting one training course per setting in each country with the intervention group (and another at the end with the wait-list group). Each cluster is expected to include approximately 20 participants. No formal pairing criteria will be applied; however, the relative homogeneity of each setting and consideration of education level are intended to contribute to comparability between groups. In addition, potential contamination of groups will be considered (eg, participants in the intervention group sharing what they learnt or training materials with participants in the control group). For example, students pursuing the same degree will be allocated to the same cluster, and participants from the same (or different) areas or facilities will likewise be grouped accordingly, in order to minimise the possibility of participants from different groups having regular contact in the course of their study or work. A summary of the number of clusters per arm, assumed cluster size, cluster types and pairing approach is provided in online supplemental table 1.

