Performance bias will be minimised by ensuring that baseline (T1) questionnaires are completed before participants are informed of their allocation to the intervention or the control group. In addition, invitations and reminders will be identical across groups at all time points. At T2 and T3, participants will be reminded to carefully complete the questionnaires. Research staff involved in participant contact will use standardised and neutral messaging with no differentiation by study arm. To reduce the influence of inattentive responding, response times will be monitored. Questionnaires completed in less than 5 min (approximately a quarter of the anticipated average completion time of 20 min) will be flagged. The proportion of such responses and their distribution across study arms and time points will be reported, and their potential influence on the results will be explored.

Outcomes are assessed using self-report measures, and self-report bias (eg, social desirability) cannot be ruled out. However, the instruments have been previously piloted and used in similar populations, demonstrating acceptable reliability.^38^ Repeated measurements over time will also allow the examination of consistency in response patterns, which will be reported.

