#### Power and sample size

According to the Shiny cluster randomised trial (CRT) calculator,^54^ with six clusters per arm (12 in total) the study will have 90% power, at a two-sided 5% significance level, to detect a standardised mean difference of 0.5 in intentions scores between intervention and control groups at 6-month follow-up. In the absence of pilot data, the sample size calculation assumed a conservative intracluster correlation coefficient of 0.05, equal cluster sizes, a correlation of 0.5 between individual measurements over time and a 30% loss to follow-up. The assumed effect size was informed by a meta-analysis of MHFA training, which found pooled effect sizes for intentions were d=0.75 immediately post training and d=0.55 up to 6 months after training.^26^

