#### Statistical analyses

Statistical analyses will be conducted by a researcher not involved in participant recruitment or intervention delivery and blinded to allocation, following intention-to-treat principles; all participants who consent to participation will be included in the analysis, regardless of intervention completion or follow-up responses. Outcomes will be analysed at the individual level (rather than cluster level). Primary and secondary data will be analysed using mixed-effects models for continuous and binary outcome variables, incorporating interactions between group and measurement occasions. This method takes into consideration the data’s hierarchical structure (ie, the correlation of measurement occasions within participants and within clusters) and uses maximum likelihood methods to generate unbiased estimates even when some participants have missing data, provided that the data are missing at random. Country and setting will be added as fixed effects. Predictors of missingness will be examined using logistic regression, and variables linked to missingness will be added to models as fixed effects. Contrasts will compare change between groups from T1 to T2 and T3. Unless there are substantial imbalances at baseline, between-group effect sizes (Cohen’s d) will be calculated by standardising the differences between follow-up scores by the pooled SD. Otherwise, Cohen’s d will be calculated by dividing the mean change in each group by the pooled SD at baseline. Statistical analyses will be conducted using Stata V.19.^57^

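### Testing change from T1 with free baseline means is valid but less precise than a common-baseline model, which this design justifies

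*Protocol article*

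**What the plan says.** The Statistical analyses section plans mixed-effects models "incorporating interactions between group and measurement occasions", fitted by maximum likelihood with all consenting participants included. The test is then fixed: "Contrasts will compare change between groups from T1 to T2 and T3". On covariates it says "Country and setting will be added as fixed effects", and variables that predict missingness are to be added. The T1 score is not listed as a covariate, and no common T1 mean is stated.

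The effect size follows a different rule: "Unless there are substantial imbalances at baseline, between-group effect sizes (Cohen’s d) will be calculated by standardising the differences between follow-up scores". If imbalance is judged substantial, d is based on mean change instead.

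The Power and sample size section powers a between-group difference of 0.5 SD at 6 months and assumes "a correlation of 0.5 between individual measurements over time". Under Data collection and measures, "baseline (T1) questionnaires are completed before participants are informed of their allocation". The Randomisation section adds that allocation stays concealed until participants have enrolled.

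**The concern.** A group-by-occasion model with a free T1 mean in each arm, tested by change from T1, is a difference-in-differences estimator. It subtracts the whole observed baseline difference between arms. Here that difference has expectation zero by design, because clusters are randomised and T1 precedes disclosure of allocation. Subtracting all of it adds noise that a model with a common T1 mean avoids, since that model removes only the part that predicts follow-up.

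The clause on substantial baseline imbalance supports the free-means reading, because a model with a common T1 mean would leave no such difference to handle. With 12 clusters there is little precision to spare. The article also tests change but by default reports d from follow-up scores, so the test and the headline effect size can come from different estimators. Which formula is used for d depends on the observed data and on a threshold the article does not define.

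**Working it through.** **Inputs from the article.** Six clusters per arm; "Each cluster is expected to include approximately 20 participants"; 30% loss, so 20 × 0.7 = 14 at T3; ICC 0.05; individual correlation over time 0.5; standardised difference 0.5; two-sided 5%.

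**Assumptions, not in the article.** The cluster autocorrelation (CAC, the correlation over time of a cluster's random effect) is varied over 0.5, 0.8 and 1.0. The 0.5 is taken as the within-person correlation after removing the cluster effect. Where a t reference is used, it has 12 − 2 = 10 degrees of freedom.

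**Step 1: completers only, closed form (m = 14).**
- Design effect: 1 + 13 × 0.05 = 1.65.
- Follow-up-only variance: v = 2 × 1.65 / (6 × 14) = 0.0393, SE 0.198.
- Correlation of cluster means over time: R = [14 × 0.05 × CAC + 0.95 × 0.5] / [14 × 0.05 + 0.95]. This is 0.500, 0.627 and 0.712 for CAC 0.5, 0.8 and 1.0.
- Change contrast: v × 2(1 − R) = 0.0393, 0.0293, 0.0226 (SE 0.198, 0.171, 0.150).
- Common T1 mean: v × (1 − R²) = 0.0295, 0.0238, 0.0194 (SE 0.172, 0.154, 0.139).
- Relative cut: 1 − (1 + R)/2 = (1 − R)/2, which is 25%, 19%, 14%.

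**Step 2: the article's 90%.** With CAC 0.8 and a common baseline, 0.5/0.154 − 1.96 ≈ 1.28, which gives 90.0% power. The change contrast in the same setting gives 83.2%. The match is not unique: 84 per arm with clustering and baseline both ignored also gives 90.0%, and 20 per cluster with no loss and a variance factor of 0.75 gives 89.3%.

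**Step 3: the analysis as described.** Maximum likelihood with all consenting participants also uses the T1 scores of those who later drop out. I solved this by generalised least squares with 20 per cluster at T1 and 14 at T3, with free and then common T1 means:

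| CAC (assumed) | Variance, free T1 means | Variance, common T1 mean | Cut | Power, normal | Power, 10 df |
|---|---|---|---|---|---|
| 0.5 | 0.0376 | 0.0295 | 22% | 73% → 83% | 64% → 75% |
| 0.8 | 0.0276 | 0.0237 | 14% | 85% → 90% | 77% → 83% |
| 1.0 | 0.0209 | 0.0190 | 9% | 93% → 95% | 88% → 90% |

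Adding T2 to the model leaves the cuts at 22%, 14% and 9%.

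**The case against.** The best defence is that nothing here is wrong. A difference in change from a mixed model is unbiased under randomisation and is a standard analysis. That stands: the point concerns precision, not validity. Change scores do over-correct a chance baseline difference, but this is an error conditional on the imbalance that happens to occur, and matching by setting should limit it.

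Second, the wording does not strictly exclude a common T1 mean. Such a model also has group-by-occasion terms, and its change contrast equals the follow-up difference. A SAP that is not shown may settle this. Free means remain the natural reading, so a clarifying sentence is still worth having.

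Third, the size depends on an autocorrelation the article does not give. The article names correlation within participants and within clusters but no cluster-by-time term. If only a plain cluster intercept is fitted, the model takes the autocorrelation as 1, where the gain is smallest and the change contrast already exceeds 90% on the normal approximation.

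A reader might infer three stronger claims that the document does not support:
- That the change contrast gains nothing from measuring T1. At a correlation of 0.5 its variance factor is 2(1 − 0.5) = 1, but that applies an individual correlation to cluster means. In Step 1 it is true only at CAC 0.5. At CAC 0.8 and 1.0 the change SEs of 0.171 and 0.150 are below the follow-up-only 0.198.
- That the cut is 14% to 25%. That range assumes completers only, whereas the plan includes all consenting participants.
- That the stated 90% presupposes baseline adjustment, so that the trial is underpowered. The 90% can be reached in more than one way, and the calculator settings are not given in full.

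**Conclusion.** The point holds as a missed gain in precision. The planned contrast is valid, but a common T1 mean is justified by design and was more precise in every scenario tried. For the analysis as described, the variance of the T3 effect falls by about 9% to 22%, and by 14% at a cluster autocorrelation of 0.8. If only completers were used, it would fall by 14% to 25%. The corresponding power gain is 2 to 10 percentage points on the normal approximation, and somewhat larger at the upper end with 10 degrees of freedom. The direction does not depend on the assumed autocorrelation or degrees of freedom, but the size does. The data-dependent choice of formula for Cohen's d is a related weakness that the same change removes.

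**What to change.** Define the primary effect as the between-arm difference at T3, with T2 secondary, from a mixed model with a common T1 mean in both arms, group-by-T2 and group-by-T3 terms, and no group main effect. Keep every participant's T1 data in the likelihood. Do the same for the continuous secondary scales measured at T1. Report Cohen's d from this same contrast, and drop the rule that changes formula on observed imbalance.

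A model with T1 as a covariate is an acceptable alternative but not an equivalent one. Participants with T1 only would then contribute nothing, which sits poorly with including all who consent, and for binary outcomes the covariate changes the odds ratio being estimated.

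The cost is a few sentences in the analysis section, with no new data and no change to the design.

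### The Cohen's d rule switches formula on observed baseline imbalance, and its second formula leaves out the comparison between arms

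*Protocol article*

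**What the plan says.** All of this stands in the Statistical analyses section of the protocol article, apart from the planning figures.

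- **Model:** "mixed-effects models for continuous and binary outcome variables, incorporating interactions between group and measurement occasions".
- **Tested contrast:** "Contrasts will compare change between groups from T1 to T2 and T3". This is a difference between arms in change from baseline.
- **Switch:** "Unless there are substantial imbalances at baseline". The article gives no criterion for substantial.
- **Formula A (no substantial imbalance):** "between-group effect sizes (Cohen’s d) will be calculated by standardising the differences between follow-up scores by the pooled SD".
- **Formula B (substantial imbalance):** d is obtained by "dividing the mean change in each group by the pooled SD at baseline".
- **Planning (Power and sample size):** "with six clusters per arm (12 in total) the study will have 90% power", for a standardised mean difference of 0.5 between arms at 6 months. The assumptions are ICC 0.05, a correlation of 0.5 over time and 30% loss to follow-up.

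**The concern.** There are four faults in the rule as stated.

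1. Formula B contains no subtraction between arms. Read literally, it standardises the change in the trained arm and, separately, the change in the control arm. The trained-arm figure then includes whatever change the controls also show.
2. Formula A has no baseline term, so any imbalance judged tolerable passes partly into d.
3. The standardiser moves from a pooled SD (occasion not given) to the pooled SD at baseline, so the unit of d depends on the branch.
4. Neither formula, as worded, is the standardised form of the contrast that is tested.

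The choice of formula is made after seeing the baseline data. The article does not say whether imbalance is judged once or for each outcome, so d values in one results table could come from different formulas. The planning section expresses both the target and the earlier evidence as d (0.5, 0.55 and 0.75), so readers will compare this trial on that scale.

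**Working it through.** **Inputs from the protocol article.** Six clusters per arm, about 20 per cluster (120 per arm), ICC 0.05, individual correlation over time 0.5, 30% loss, target 0.5.

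**Assumed, not in the document.** Cluster autocorrelation (CAC) from 0.5 to 1.0, and a control-arm change of 0.15 SD.

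**The plan's own figure.** With m = 14 after loss and CAC 0.8:
- cluster-mean correlation R = (14×0.05×0.8 + 0.95×0.5)/(1 + 13×0.05) = 1.035/1.65 = 0.627
- SE² = (2/84)×1.65×(1 − 0.627²) = 0.0238, so SE = 0.154
- power for 0.5 = Φ(0.5/0.154 − 1.96) = 0.90

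The stated 90% can therefore be reproduced under an unstated CAC. This point does not depend on it.

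**How often the switch is in play.** SD of the baseline difference = sqrt((2/120)×(1 + 19×0.05)) = sqrt(2×1.95/120) = 0.180.

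| Threshold for substantial (SD) | Chance of exceeding it |
|---|---|
| 0.1 | 58% |
| 0.2 | 27% |
| 0.3 | 10% |

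These figures give no credit for pairing. At ICC 0.02 the SD is sqrt(2×1.38/120) = 0.152, and 0.2 is exceeded in about 19% of trials.

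**What formula A carries.** At m = 20, R = (20×0.05×CAC + 0.475)/1.95, which is 0.50 at CAC 0.5 and 0.76 at CAC 1.0. A baseline difference of 0.2 SD adds 0.2×0.50 = 0.10 to 0.2×0.76 = 0.15 to d, in the direction of the imbalance.

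**Formula B read literally.** With a true between-arm effect of 0.50 and a control change of 0.15, simulation (8,000 trials per scenario) gives about 0.66 for the trained arm and 0.15 for controls. Neither is 0.50; their difference is.

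**Formula B read as a difference in changes.** For the same participants and the same SD, (follow-up difference) − (difference in changes) = baseline difference. At a 0.2 SD imbalance, the choice of formula alone moves d by 0.2, which is 0.2/0.5 = 40% of the target.

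**Simulated mean d, true value 0.50** (ranges cover CAC 0.5 and 1.0):

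| Estimator and baseline difference | Favours MHFA | Favours control |
|---|---|---|
| Formula A, 0.1 to 0.2 SD | 0.57 to 0.62 | 0.39 to 0.43 |
| Baseline-adjusted, 0.1 to 0.2 SD | 0.50 to 0.54 | 0.47 to 0.50 |
| Formula B as difference in changes, beyond 0.2 SD | 0.36 to 0.43 | 0.58 to 0.64 |
| Baseline-adjusted, beyond 0.2 SD | 0.50 to 0.57 | 0.44 to 0.50 |

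The two formulas err in opposite directions. At CAC 1.0 the simulated adjustment removes only part of the imbalance.

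**Averages and precision.** Over all trials, every between-arm estimator averages about 0.50. The SD is about 0.18 for formula A and 0.13 to 0.16 for the adjusted estimate. Formula A confined to trials within 0.2 SD of balance has SD 0.15 to 0.165; confined to within 0.1 SD, it has 0.13 to 0.16. The precision gain from adjustment therefore depends on where the undefined threshold falls.

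**The case against.** The best defence is that d is a supplementary summary. Tests rest on the mixed-model contrasts, and no p-value or power claim depends on this rule. That stands.

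Formula B also has a natural between-group reading: it continues a sentence about between-group effect sizes and follows one about change between arms. A difference in changes may well be intended. That is plausible, but the text does not say it, and on that reading the switch still moves d by the full baseline difference.

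A numerical definition of substantial may sit in an analysis plan not shown here, and the analyst is to be blinded to allocation. Both are fair, so the missing threshold is not itself the fault. The fault is that the article fixes a rule with two different estimators.

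Four stronger readings are tempting, and the document does not support them.

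- **That formula A is confounded by baseline.** Clusters are randomised, and formula A averages the true effect. What remains is chance error in either direction, so deflation is as likely as inflation.
- **That d uses completers only.** The text does not say whether the follow-up scores are observed or model-estimated.
- **That d cannot be compared with the planned 0.5.** The planned target is itself a between-arm standardised difference at 6 months, which is the formula A quantity.
- **That d is the headline result.** The article does not give it that status.

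**Conclusion.** The point holds for the reported standardised effect size and not for the hypothesis test. Formula B needs correcting as worded, whatever was intended. The switch makes d depend on observed imbalance, with a shift equal to the baseline difference if formula B means a difference in changes. That shift has an SD of about 0.18 and exceeds 0.2 in about 27% of trials. Where formula A is kept, a 0.2 SD imbalance carries about 0.10 to 0.15 into d.

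The 0.18 and 27% rest on the plan's ICC of 0.05, which it calls conservative, and on clusters of 20; both fall with a lower ICC or if pairing by setting and country works. The 0.10 to 0.15 rests on an assumed cluster autocorrelation of 0.5 to 1.0. The 0.66 and 0.15 rest on an assumed control change. The change should be made, but the trial's main inference does not hang on it.

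**What to change.** Delete the switch and both formulas. Prespecify one d for every outcome on a continuous scale, whatever the observed imbalance: the mixed model's between-group contrast at T2 and at T3, divided by the pooled T1 SD, with its confidence interval from that model.

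The contrast should preferably be baseline-adjusted, for example by constraining the arms to a common baseline mean. The same model must then serve the test, so that d and the test agree. If the planned difference in change is kept for the test, d should be that contrast divided by the pooled T1 SD.

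The cost is two replaced sentences, plus a change to the contrast sentence and the model description if the common-baseline form is adopted. No new data and no design change are needed. The change should be recorded before outcome data are analysed.

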### Patient and public involvement statement

Individuals with lived experience of mental ill-health, either personal or as informal caregivers, were involved as members of expert panels advising on the suitability of mental health first aiders receiving (or not receiving) training on specific topics during the development of the guidelines that informed the cultural adaptation of the MHFA training course.

## Ethics and dissemination

Ethics approval has been obtained from the Human Research Ethics Committee at the University of Melbourne (Reference: 2024-30813-59250-3, 17 October 2024, V.3), the Ethics Committee of Proyecto Suma (#2024–14006) and by the Ethics Committee of the University of Chile (#74-89/2024). Any substantial amendment to the protocol will be submitted for ethical review as required.

Dissemination will be via academic publications and conference presentations. These will also be made available to participants and other interested parties on request. The questionnaire used for data collection will likewise be available on request. The university website and MHFA International’s dissemination channels will also be used. Authorship will follow established international guidelines for responsible research conduct.

## Discussion

Findings from this trial will examine whether MHFA training for Chile and Argentina enhances intended support, knowledge, attitudes and supportive actions towards a person developing a mental health problem or experiencing a mental health crisis in these countries. Since there is no prior experience with delivering an MHFA training in these countries, except for the pilot experience mentioned above, the current trial addresses a major gap in knowledge. Furthermore, given their shared historical and cultural roots, coupled with their divergent paths in mental health reform, Argentina and Chile present a compelling opportunity for a collaborative endeavour. By studying the effectiveness of MHFA training across both nations, we hope to gain valuable insights into the applicability and potential adaptations required for such interventions to succeed in diverse societal contexts. Ultimately, this may benefit the well-being of people with mental health problems in Chile and Argentina, strengthen the connection between formal and informal care while enhancing informal support, and reduce the related burden of disease associated with mental health in these (and potentially other) countries.
